### Health education intervention

Group A will receive health education through WeChat at 8.00 p.m. every 2 days. A previous study [37] has proven that WeChat push frequency has an impact on information dissemination. When the WeChat platform is used to provide education regarding edible oils, attention should be given to the time and frequency of intervention to avoid inciting negative behaviour among the participants. Thus, we will provide intervention every 2 days. Previous studies [38] have confirmed that the rate of reading articles published on WeChat accounts peaks at 9.00 p.m., and thus, we will publish the content at 8.00 p.m. to allow subjects to better accept the intervention and help us improve its effectiveness. Moreover, we will collect weekly feedback from the participants using two self-designed questions through WeChat: ‘Are you interested in the contents this week?’ and ‘What do you suggest for next issue’s content?’ The feedback will help us assess the satisfaction of the participants, and consequently, improve the contents and methods of intervention.

In accordance with the Chinese Dietary Guidelines [10] and the Chinese Dietary Reference Intakes, health education can be provided through lively presentations with text, images, videos and audios. The WeChat public platform will be used as the communication tool of the intervention group for 4 weeks. Content will include information regarding the negative effects of excessive edible-oil intake, facts about edible oils, suggested reasonable amounts of edible-oil intake and lectures on healthy oil use guidelines provided by nutrition experts. Information about the differences between saturated and unsaturated edible oils (Table 2) and their composition and nutritional properties will be provided to aid in edible-oil selection according to individual needs. Questions for increasing public interaction will also be included, such as ‘Did you control your oil intake today?’ and ‘Do you pay attention to your edible-oil intake?’ An interactive platform will be set up to allow nutrition experts to answer participants’ questions in real time. The process will last for 4 weeks, and the intervention effects on edible-oil usage will be evaluated immediately, 3 months and 6 months after intervention.

**Table 2 Tab2:** Fatty acid composition of common edible oils (%)

	Saturated fatty acid	Monounsaturated fatty acids (ω-9)	Polyunsaturated fatty acids		Trans fat
			Linoleic acid (ω-6)	Alpha-linolenic acid (ω-3)	
Olive oil	15	75	9	1	ND
Soybean oil	15	23	53	8	1
Canola oil	7	61	21	11	ND
Peanut oil	19	48	32	ND	0.6
Nutritional blend oil	9	28	60	ND	2
Lard	43	44	9	ND	ND

Note: ‘ND’ denotes no detection, and the content is below 0.05% [40]

### Knowledge, attitude and behaviour tests

The knowledge, attitude and behaviour tests will consist of two parts: a knowledge and attitude questionnaire survey and a behaviour test on edible-oil intake. The knowledge, attitude and behaviour tests will be administered to each participant during three face-to-face visits: immediately, 3 months and 6 months after intervention.

#### Knowledge and attitude questionnaire

Participants will answer a self-designed questionnaire, which includes knowledge regarding edible oils and intake attitude. The questionnaire is designed based on KAP, and it contains 30 items with only one correct answer. Each question is equivalent to 1 point. A high score corresponds to excellent knowledge and a positive attitude regarding edible-oil intake. Changes in participants’ knowledge and attitude will be assessed based on their final score.

#### Edible-oil intake behaviour test

Data on edible-oil intake will be obtained by conducting a continuous 3-day weighing survey on households, i.e. investigating the consumption of various edible oils within a family for 3 days. The survey time includes two working days and one rest day [39]. We will use the SF-400 kitchen scale (a calibrated bench-top scale; the maximum allowable amount is 5 kg and the sensitivity is 1 g) to measure the consumption of household edible oils [39]. The survey respondents are all household members and guests who consume cooking oil and condiments in the surveyed households. The daily consumption of individual edible oils is obtained using a family oil estimation algorithm. The decrease in the participants’ use of edible oils will be assessed according to the obtained data.

Daily consumption of oil intake estimates of each inhabitant (g/standard) = (3 days’ intake of edible oils by the surveyed households × standard daily number of people in a survey per household/standard number of people in all households)/3 [40].

### Quality control

To ensure the reliability of the survey data, the intervention programme will be established by the Department of Nutrition and Food Hygiene, School of Public Health and Management, Chongqing Medical University. The reliability and validity of the baseline and knowledge and attitude questionnaires will be tested.

A study manual will be provided before the survey, and training will be conducted among all the investigators. A standardised face-to-face questionnaire will be administered to the participants through the appropriate implementation and application of the unified method. Standardised experimental equipment and measurement methods will be used in the study, and kitchen scales will undergo quality control. To ensure that the weighing results of home cooking oil are accurate and reliable, the weighing range of the kitchen scales used in the survey will be set to 0–5 kg, with an accurate value of 1 g.

### Data management and entry

All the questionnaires will be collected, stored in a single file and regularly checked and rechecked. The questionnaires will be encoded and entered in a timely manner using the EpiData 3.1 double-entry test results.

### Analysis strategy

Statistical analyses will be conducted using IBM SPSS Statistics (version 22.0). Descriptive statistics will be calculated for all the variables under examination. Anthropometric measurements at the baseline will be analysed to examine the influence of the factors on edible-oil intake behaviour via multivariate regression analysis, with age, occupation and education level included in the model.

## Discussion

In accordance with the experiment design, the intervention group will receive 4 weeks of intervention to determine whether differences in edible-oil knowledge and intake behaviour exist between the intervention group and the control group. The experimental design will ensure balance among the confounding variables in each group and will eliminate the bias caused by the characteristics of the participants. Given that the enrolled participants should be good at using the WeChat app, the samples will exhibit this bias from the beginning. To avoid potential biases during the entire process, we will strictly follow the inclusion criteria when recruiting participants and use blind methods to collect data during the implementation phase. In addition, to increase the participation rate and reduce the selection bias, we will use children’s health as an entry point. Given that the participants are women between the ages of 25 to 45 years, most of them will have children in their family. In China, children are considered ‘emperors’ in the family. Most women care about their children’s health; thus, we will provide knowledge about edible-oil consumption among children during the intervention.

This study aims to encourage participants to decrease their use of edible oils and change their unhealthy behaviour. We hypothesise that group A will have higher awareness and willingness to decrease their use of edible oils than group B, which will indicate that the intervention based on social cognitive theory is effective. Moreover, the knowledge and attitude of participants will improve immediately after the intervention but will decrease considerably after 6 months. Such results would imply that the immediate effect of the intervention would provide the best results, whereas the long-term effect would be poor. Moreover, we believe that the intervention results may be affected by the duration of the intervention, as confirmed in previous studies [41]. A short intervention may show that the effect is inevident. In such a case, we can appropriately increase the duration of intervention in the follow-up study. Moreover, the traditional ideas of the participants are ingrained; even if they know that the excessive consumption of saturated edible oils are among the risk factors of chronic diseases, they will still not reduce their intake. A previous study [42] has confirmed that an increase in health knowledge is not always accompanied by changes in unhealthy behaviour and the transition from the intention stage to the action stage will take time. We speculate that this condition may also affect the outcome of our intervention. In addition, we speculate that the participants’ habits and economic status may also influence their edible-oil intake behaviour.

### Strengths and weaknesses

The present study exhibits strengths and weaknesses. This work will be the first intervention that will attempt to reduce the use of edible oils in China through WeChat. Moreover, the adoption of the three models, namely, KAP, social cognitive and SOC theories, will allow us to address the limitations of each model. The limiting factors of this study include the intervention that focusses on the family’s dietary decision-maker (i.e. housewives), without providing health education intervention to all family members. In addition, given the wide-spread use of WeChat, the participants may transmit the intervention to other people, through the app, without our permission. Therefore, we cannot guarantee that each participant in the control group will not receive knowledge regarding edible-oil intake from other sources during the intervention period.

In conclusion, this study should provide guidance on family health education and behaviour intervention regarding edible oils by increasing housewives’ knowledge regarding edible oils and encouraging them to use edible oils scientifically to promote overall health. This study can also be used as a reference for foreign studies. Through the evaluation of the intervention effects, changes in knowledge and behaviour regarding the edible-oil intake of the participants who received health education will validate our hypothesis and may encourage public officials to focus on health education and realise the value of the WeChat platform.

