### Participants and recruitment

Participants will be recruited from the following four areas (rural and urban) in Chongqing, China: Yuzhong District, Shapingba District, Dianjiang District and Wulong District. Each district represents a different level of economic development.

A publicity group will be set up during the early stage of the project. An advertisement with a short comic strip will be designed to present the study, and printed posters and leaflets will be disseminated in the cooperating communities. Women who are interested can register at the community centre. Community leaders can, if they find it appropriate, inform them about the possibility of participating in the study. Recruitment will also be done through announcements on microblogs and WeChat. Women who wish to participate will have to provide their informed consent and enrol on the study’s homepage if they meet the inclusion criteria.

The inclusion criteria are as follows: women who are between the ages of 25 and 45 years, involved mainly in housework (particularly cooking) and active daily users of WeChat (i.e. using WeChat more than three times daily).

The exclusion criteria are as follows: individuals who have never cooked, have been involved in other edible-oil experiments and those with cognitive or verbal impairments or diseases that require them to follow strict diets.

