### Study procedure

This study uses a combination of primary and secondary data. The quantitative cross-sectional studies will last for 4 weeks and will use WeChat as an intervention tool. A total of 800 housewives between the ages of 25 to 45 years will be recruited from different communities in Chongqing, China. A status survey will be conducted from September 2019 to November 2019. A previous study [36] has proven that age and education are associated with edible-oil intake behaviour. To eliminate the influence of confounding factors, 200 housewives with similar ages and educational levels will be selected to participate in a baseline survey. Subsequently, they will be divided randomly following a 1:1 ratio into an intervention group (group A) and a control group (group B) using computerised simple randomisation in SPSS. In the next 4 weeks, group A will receive health education through WeChat every 2 days, whereas group B will receive nothing. Each participant will then be given knowledge, attitude and behaviour tests immediately (immediate effect), 3 months (short-term effect) and 6 months (long-term effect) after the intervention. In accordance with the SOC model [35], the entire process of changing edible-oil intake behaviour among the housewives will be divided into six stages (Table 1). In addition, the changes in their behaviour stages and influencing factors will be analysed to evaluate the effects of the intervention on edible-oil intake. All subjects will read and sign a written informed consent form before their voluntary participation.

**Table 1 Tab1:** Description of intervention methods corresponding to different stages

Stages	Intervention focus
Precontemplation	Spread the knowledge and benefits related to healthy oils
Contemplation	Encourage them to start trying to control oil intake
Preparation	Guide participants on how to use edible oils in a healthy manner
Action	Help participants identify factors that affect their persistence in decreasing oil intake
Maintenance	Self-motivation
Termination	\

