### Randomisation and blinding

After the status survey, 200 housewives with similar ages and educational levels will be selected and divided randomly following a 1:1 ratio into an intervention group and a control group using SPSS. The study coordinator will be responsible for the randomisation and verification of the computer-generated treatment assignment with a randomisation table. All the investigators, except for the study coordinator, will be blinded. The participants will be instructed not to inform the other participants of their group assignment.

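### The plan concedes that content may be forwarded to controls, but its stated instruction to participants covers group assignment only, and its caveat covers only the intervention period

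*Protocol article*

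**What the plan says.** All references are to the Protocol article.

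- **Channel** (Health education intervention): "The WeChat public platform will be used as the communication tool of the intervention group for 4 weeks". Content goes out every 2 days. The section does not say who can open the account.
- **Allocation** (Study procedure): the 200 women are "divided randomly following a 1:1 ratio into an intervention group (group A) and a control group (group B) using computerised simple randomisation in SPSS". The unit is the individual woman.
- **Recruitment** (Participants and recruitment): "printed posters and leaflets will be disseminated in the cooperating communities", and women can register at the community centre. There is also an online route: "Recruitment will also be done through announcements on microblogs and WeChat". The inclusion criteria require every participant, in either arm, to use WeChat more than three times a day.
- **Instruction to participants** (Randomisation and blinding): "The participants will be instructed not to inform the other participants of their group assignment".
- **Acknowledged limitation** (Strengths and weaknesses): "the participants may transmit the intervention to other people, through the app, without our permission", so that "we cannot guarantee that each participant in the control group will not receive knowledge regarding edible-oil intake from other sources during the intervention period".
- **Timing** (Study design): tests take place immediately, 3 months and 6 months after the 4-week intervention. Controls are given the material only once the 6 months of follow-up are over.

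**The concern.** The stated instruction and the acknowledged risk do not meet. The instruction stops a woman from saying which group she is in. The risk is that she passes on a post. She can obey the instruction to the letter and still forward everything she receives.

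The caveat is also narrower than the period that matters. It refers to the intervention period, but two of the three comparisons fall 3 and 6 months later. The Background section lists repeated viewing among the features of WeChat, and nothing in the article says that posts are withdrawn after week 4.

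Exposure of controls would pull the arms together. The Discussion already foresees a weak or fading effect. It puts this down to short duration and ingrained habits, and suggests a longer intervention in a later study. If exposure of controls were part of the cause, that remedy would miss it. Repeated testing can also raise control scores, so an improvement in group B would not by itself reveal exposure.

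**Working it through.** **1. The plan's own figure.** Sample size calculation and participants gives N = Z²pq/d². With Z = 1.96, p = 0.8, q = 0.2 and 0.08 in the denominator, 3.8416 × 0.16 / 0.0064 = 96.04, which reproduces. This is the precision of a single survey proportion. It contains no difference between arms, no power and no allowance for exposed controls, so the 200 randomised women carry no stated margin for dilution.

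**2. Instruction against risk.** Protected: group assignment, towards other participants. Conceded as at risk: content, towards anyone reachable through the app. The stated instruction does not cover the conceded risk.

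**3. Period covered against period needed.** Covered by the caveat: 4 weeks. Needed: 4 weeks plus 6 months, or about 4 + 26 = 30 weeks.

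**4. Size of the dilution.** The article gives no exposure rate, effect size or power, so everything in this step is a scenario. Let c be the share of controls exposed and r the fraction of group A's response that an exposed control shows. The difference left is (1 − rc) of the true one, and the sample needed to keep the same power grows by 1/(1 − rc)². For power, take 100 per arm, two-sided alpha 0.05, and a true effect that would have 80% power without exposure: (1.96 + 0.8416) × √(2/100) = 0.396 SD. Power is then Φ(2.8016 × (1 − rc) − 1.96).

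| c | r | Effect left | Sample factor | Power |
|---|---|---|---|---|
| 0 | – | 100% | 1.00 | 80% |
| 10% | 1 | 90% | 1.23 | 71% |
| 20% | 1 | 80% | 1.56 | 61% |
| 30% | 1 | 70% | 2.04 | 50% |
| 10% | 0.5 | 95% | 1.11 | 76% |
| 20% | 0.5 | 90% | 1.23 | 71% |
| 30% | 0.5 | 85% | 1.38 | 66% |

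Example for c = 20%, r = 1: 1/0.8² = 1.56, and 2.8016 × 0.8 − 1.96 = 0.281, so power is 61%.

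A binary outcome behaves much the same. Starting from the plan's 80% with excess intake in controls, and from the group A proportion that gives 80% power with 100 per arm (62.1%), power at r = 1 is 70, 59 and 48% for c = 10, 20 and 30%.

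**The case against.** The strongest reply is that the authors have already said this. They name the route and the consequence, and the article does not contradict itself. That stands: the risk was not overlooked. But disclosure neither reduces the bias nor helps a reader judge its size afterwards.

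Several stronger readings are tempting, and the article does not support them:

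- **That exposure goes unmeasured.** The questionnaires and the study manual are not shown. The weekly feedback questions that are quoted ask about interest and suggestions, but an exposure item could exist elsewhere.
- **That anyone can open the account.** The name of the platform suggests this, but access is not described and may already be restricted.
- **That the authors expect forwarding.** They say it may happen. Their remark that it would be without permission even suggests that it is not allowed, although no such rule is stated.
- **That all the women share communities.** Some are recruited online, across four districts. How many know one another is unknown.
- **That the r = 1 rows are a forecast.** Group A receives a series of posts, stage-specific strategies and answers from nutrition experts. A forwarded post is much less than that, and the Discussion itself doubts that knowledge alone changes behaviour. Dilution of the weighed oil intake could therefore be small.

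The bias also runs mainly towards no difference. A positive result would not be undermined; a weak or null one would be harder to read.

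**Conclusion.** The point holds as a modest, cheaply closed gap. Two things rest on the text alone: the stated instruction leaves content sharing uncovered, and the caveat covers about 4 of the roughly 30 weeks in which controls must stay unexposed. With individual allocation among daily WeChat users recruited partly through shared communities, exposure of controls may dilute the difference between the arms by an unknown amount.

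If 10, 20 or 30% of controls responded fully like group A, 90, 80 or 70% of the effect would remain. Those are the lowest values for each share, because a partial response leaves more. Both the shares and the full response are assumptions, and the power figures also assume an effect that has 80% power without exposure. A reader might infer that a null result would show contamination. The article does not support that; the two would simply be hard to tell apart unless exposure is recorded.

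**What to change.** 1. Extend the instruction under Randomisation and blinding: participants should not forward or show study content to people outside their household until the 6-month visit. Cost: one sentence.
2. State who can open the account and, if this is not already done, limit access to group A's registered WeChat IDs. Cost: an account setting.
3. If the questionnaires do not already contain them, add one or two items to each of the three visits asking both arms whether they saw or shared the content. Report exposure by arm beside the as-randomised result. Cost: a slightly longer questionnaire. The items may prompt controls, so place them last.
4. Reword the caveat under Strengths and weaknesses so that it runs to the 6-month test.

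Randomisation, sample size and outcomes stay as they are. Whether to add an analysis adjusted for exposure is a matter for the analysis plan, which is not shown.

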### Trial status

The recruitment phase of this study is scheduled from May 2019 to August 2019. Health education intervention will be conducted for 4 weeks for each participant. Follow-ups will be conducted over 6 months. Data analysis and evaluation will be performed after 12 months. The final results of this study will then be published.
